**Study Visits** (Figure 6). After randomization, all subjects will return once a week for the first two weeks, then at week 4. From this point forward, subjects will be seen every 4 weeks until study completion. The visit window is plus or minus 3 days, except for the day 7 visit (+1) for STAGE 1 participants, calculated from the Baseline visit (Day 0). At every study visit participants will be seen for assessment of vital signs, adverse events, and concomitant medications. Urine will be collected and safety laboratory studies will be drawn at screening, weeks 1, 2, 4, and at every study visit following week 4. Study drug accountability and compliance will be assessed at every study visit. The ALSFRS-R will be completed at the screening visit, Week 4 and every 8 weeks starting at week 16. Subjects will have an abdominal ultrasound performed at weeks 4, 8, and 20 to monitor for biliary disease. If there is evidence of biliary disease, the site will repeat the ultrasound as clinically necessary until this condition has resolved. Muscle strength testing, VC, quality of life questionnaires, weight and plasma samples for trough ceftriaxone levels will be obtained every 16 weeks for study duration.

Blood for ceftriaxone levels will be drawn in the morning, prior to first dose. The subjects may receive their first dose at the clinic. This will serve as another opportunity to monitor how the caregiver administers the study drug. At each visit, subjects will be monitored for problems with self-administration of study drug as well as for evidence of drug reaction or skin infections at the central venous catheter site.

**Missed Visits.** When a subject fails to appear for a scheduled visit, the site should contact the subject and a partial evaluation may be performed over the telephone, or if possible by a visit to the subject's home. If a subject is evaluated by telephone, the following information should be

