obtained: vital status, adverse events, ALSFRS-R, review of ventilator status and mechanical ventilation record and study drug compliance check. The site should stress that safety labs are critical, and should strongly encourage the subject to report to a clinical laboratory designated by the central clinical laboratory to have safety laboratory studies performed. If either a telephone contact or a home visit is made, an additional supply of study drug may be dispensed. The subject should be strongly encouraged to appear for the next scheduled evaluation. Site staff are encouraged to be willing to travel to the participant if needed.

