#### **STAGE 3**

**Primary Outcome measures.** Co-primary outcome measures include survival, defined as time to death, tracheostomy or the initiation of permanent assisted ventilation (PAV) and change in function as measured by ALSFRS-R. Non-invasive ventilation techniques utilized for more than 22 hours daily for more than one week will be the criterion for determining PAV. The primary analysis will be by "intention to treat." We will ascertain the status of all subjects at the end of the study and every subject will be included in the analysis whether or not they elected to stop treatment before the end of the study. The analysis of survival will use a log-rank test stratified by riluzole use. The use of the log-rank test and a design where everyone is treated until the end of the study has several advantages over treating everyone for only 52 weeks and using the 52-week mortality. By enrolling subjects at a constant rate in over an approximate 24-month enrollment period, we will be able to follow subjects anywhere from 12-36 months, with an average of 18 months of on-treatment follow-up. This is close to estimated median survival time found in previous ALS studies [95]. The power of tests comparing survival distributions depends on the number of events during the trial. Thus there are substantial power advantages

for treating people for a longer duration. To examine the co-primary endpoints jointly, our primary analysis strategy is to use the “shared parameter” model described in Vonesh, Greene and Schluchter[148]. This is described in more detail below in Section 9.1.3. The data analysis will be based on the ALSFRS-R during the first 12 months of treatment.

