### ***Stopping for Efficacy***

Efficacy stopping will use the alpha spending rule approach which allows flexible choice of monitoring times. The basic idea is that the trial can “spend” (or allocate) a one-sided Type one error of 0.025 (equivalent to a two-sided  $p=0.05$  test) over the course of the trial. Thus one can pre-define a “spending” function which gives the amount of alpha spent as a function of the proportion of the total number of events that have occurred by the time of the interim analysis. We will schedule the interim analyses as defined below with an alpha spending function which depends on the proportion of events, denoted by  $t$  (so called information time), that has occurred by that analysis. The alpha spending function we will use is  $0.025 t^3$ . We will assume that the total number of events on the trial will be 293, this is the number expected based on a yearly survival rate of 75%, for the purposes of computing  $t$  although this may be adjusted using the guidelines in Proschan, Lan and Wittes [187]. The table below gives the efficacy stopping guidelines for the trial based on our assumptions about the accrual and mortality rate. The two event rate estimates are calculated under the alternative and null hypothesis assuming a one year survival of 75%. We assume that the accrual will take five months to ramp up to 25 patients per month. The  $p$ -value to stop is one-sided. The first meeting three months after the start of accrual for STAGE 3 (Study Month 3) will have the purpose of reviewing the safety of Ursodiol use and any other new procedures of the STAGE 3 portion of the study.

| Study Month | Accrual | Number of Events | $p$ -value to stop |
|-------------|---------|------------------|--------------------|
| 3           | NA      | NA               | NA                 |
| 9           | 235     | 31-40            | 0.000064           |
| 15          | 385     | 61-75            | 0.000374           |
| 21          | 535     | 102-125          | 0.001686           |
| 27          | 600     | 153-187          | 0.005537           |
| 33          | 600     | 201-244          | 0.011807           |
| 39          | 600     | 243-293          | 0.019872           |

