### ***Analysis of ALSFRS-R***

Our primary analysis strategy is to use the “shared parameter” model described in Vonesh, Greene and Schluchter, 2006 [148]. They propose a random effects analysis of variance to model

the change in ALSFRS-R over time. The basic idea of this model is that each subject has his or her own trajectory with a random slope, intercept and curvature, the average value of which may depend on treatment. The primary analysis of ALSFRS-R will include measurements made during the first 12 months only, to minimize the effect of drop out. They extend this model to include a parametric model for mortality during the 12 month period that we are analyzing. This corrects the estimate of the treatment effect for loss of data which might be dependent on the subject's ALSFRS-R trajectory. We will model survival by assuming that the mortality distribution is Weibull with a scale parameter that depends on the random slope and intercept of ALSFRS-R. We plan to continue follow up of subjects who discontinue treatment so that we should have ALSFRS-R at all of the time-points on the vast majority of subjects except for those that die. As a sensitivity analysis, we will also correct for subjects who are missing their final ALSFRS-R measurements using a modification of the model described above. This model can be modified by having two causes of "failure", death and "missing further data". Then both of these outcomes can be modeled using a Weibull model as above and the difference in the slopes due to treatment can be calculated, corrected for dropouts and deaths which may be associated with ALSFRS-R.

The primary analysis will use a p-value of 0.05. There will be no efficacy stopping boundaries for ALSFRS-R. We don't include an efficacy stopping boundary for ALSFRS-R because if ALSFRS-R is strongly positive it will indicate that with enough follow up and subject accrual we may eventually see a survival benefit. Since measuring the survival benefit, if there is one, is a primary goal of the trial we would not want to stop the trial if there is a good chance of seeing a survival benefit. Futility boundaries are described below. With the sample size of 600 subjects and a 2:1 randomization we will have 80% power to see a 25% decrease in the rate of ALSFRS-R decline in either treatment group.

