### *Analysis of Secondary Outcome Variables*

**Safety and Tolerability.** The safety data will be summarized by treatment group. The treatment groups will be compared with respect to occurrence of each adverse event. Total number of adverse events and abnormal laboratory tests will be compared between groups using Fisher's exact test. Withdrawal, abnormal laboratory tests, vital signs and use of concomitant medications will be assessed to characterize the safety profile of ceftriaxone. Compliance data will be determined for each visit and by treatment group. The time to subject refusal will be compared between treatment groups in order to better determine tolerability. This will be accomplished using a method of survival analysis that allows informative censoring due to death [188]. Descriptive statistics denoting the changes from baseline to the final assessment visit with respect to key laboratory parameters and vital signs will also be provided.

**VC, Dynamometry and Quality of Life.** Our primary analysis strategy is to use a random effects analysis of variance using PROC MIXED in SAS [189]. The basic idea of this model is that each subject has his or her own trajectory with a random, slope, intercept and curvature the average value of which may depend on treatment. Since the subject groups start out the same, the intercept will not depend on treatment but the slope and curvature may. In our trial of topiramate this model was sensitive to a negative effect on muscle strength on treatment.

There was a significant curvature but only the slope was affected by treatment. The advantage of using this model is that it accommodates the variable duration of follow-up that will result from our trial design. We will look carefully at the residuals for this model to be sure that it fits the data. If there appear to be problems with fit, we will use a robust approach of assessing significance where the p-value for any treatment contrast is calculated using a permutation test.

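### Vital capacity and hand-held dynamometry slopes are analysed with no allowance for slope-dependent death, so a real benefit on them could be understated by roughly 6–24%

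*Combined protocol and SAP*

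**What the plan says.** Section 9.1.3, Analysis of Secondary Outcome Variables, covers VC, dynamometry and quality of life together: "Our primary analysis strategy is to use a random effects analysis of variance using PROC MIXED in SAS". Each subject has a random intercept, slope and curvature, and treatment may alter slope and curvature. The stated merit is: "The advantage of using this model is that it accommodates the variable duration of follow-up that will result from our trial design". The only fallback is a permutation test, used if residuals show poor fit. No data window, death term or missing-data analysis is named. The section claims 80% power at two-sided 0.05 for a 17% slower decline, using placebo-group parameters from a 12-month topiramate study.

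Section 9.1.3, Analysis of ALSFRS-R, treats the same kind of slope differently. "The primary analysis of ALSFRS-R will include measurements made during the first 12 months only, to minimize the effect of drop out". The slope model is extended with Weibull mortality that depends on the subject's random slope and intercept, and a further sensitivity analysis handles dropout.

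On schedule and follow-up, section 6.2.2 says that muscle strength, VC and quality-of-life measures "will be obtained every 16 weeks for study duration". Section 6.3.4, STAGE 3, says "we will be able to follow subjects anywhere from 12-36 months". On deaths, Stopping for Efficacy says "We will assume that the total number of events on the trial will be 293", and its table gives 243–293 events at month 39, the lower figure under the alternative.

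**The concern.** The plan accepts that death can distort a slope comparison for ALSFRS-R, then says nothing about it for two outcomes that it links to survival itself. Section 2.1.1 lists rate of respiratory change among the significant covariates of survival. Section 6.3.4 calls strength a likely determinant of survival.

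The mechanism is as follows. Fast decliners die after few visits. Their slopes are then poorly estimated, and the mixed model shrinks them towards their arm's average. If death depends on the true slope beyond what the observed values reveal, each arm's decline looks too shallow. The error is larger in the arm that loses more fast decliners. With an effective drug that arm is placebo, so the treatment difference shrinks. The permutation fallback changes how the p-value is obtained and does not correct a biased slope.

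At stake are the power of the VC and strength comparisons and their interpretation, including the planned work on VC and dynamometry as surrogates for survival.

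**Working it through.** **1. The plan's event figures.** 243/600 = 40.5% under the alternative and 293/600 = 48.8% under the null. An exponential model (75% one-year survival, hazard ratio 1.5, 2:1 allocation, 60 roll-over subjects, five-month ramp to 25 per month) gives 236–285 events at month 39 if roll-overs bring no prior follow-up and 244–294 if they bring 18 months. This reproduces 243–293 within 3%. The survival power also agrees: Φ(√(243 × 2/9) × ln 1.5 − 1.96) = Φ(2.98 − 1.96) = 84.6%, against a stated figure of over 80%.

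**2. The plan's secondary power.** No SDs are printed, so the 17% figure cannot be rebuilt, but it can be inverted. The relative standard error is 0.17/(1.96 + 0.842) = 0.0607. Dividing by √(1/400 + 1/200) = 0.0866 gives an effective slope SD of 0.70 times the mean slope, measurement error included.

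**3. Size of the attenuation (simulation).** From the documents: 2:1 allocation, visits at baseline, week 4, week 16 and every 16 weeks thereafter, one-year survival of 75% (placebo) and 83% (drug), and true slowing of 17%. Assumed: slope −2.5 per month on a VC-percent scale, slope SD/mean of 0.5 or 0.65, residual SD of 4 or 8, follow-up uniform over 15.4–39 months, and a log-hazard linear in the subject's true slope. The fitted model has random intercept and slope, a fixed quadratic and treatment-by-time. Bias is measured against the same fit with no deaths and is shown as a percentage of the true effect. Power is for N = 600.

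| SD/mean | Residual SD | Hazard ratio per SD of faster decline | Bias, all follow-up | Bias, 12 months | Power %: no death / all / 12 months |
|---|---|---|---|---|---|
| 0.50 | 4 | 1.0 | +0.7 | +1.3 | 97.3 / 95.3 / 94.1 |
| 0.50 | 4 | 1.5 | −5.9 | −4.5 | 97.3 / 93.2 / 92.1 |
| 0.50 | 4 | 2.0 | −9.8 | −8.4 | 97.3 / 92.0 / 90.6 |
| 0.50 | 4 | 3.0 | −15.9 | −15.7 | 97.3 / 90.0 / 87.3 |
| 0.65 | 4 | 1.0 | +0.6 | +1.4 | 85.2 / 81.2 / 80.1 |
| 0.65 | 4 | 1.5 | −8.4 | −7.5 | 85.5 / 74.7 / 73.6 |
| 0.65 | 4 | 2.0 | −12.0 | −10.5 | 85.1 / 72.3 / 71.5 |
| 0.65 | 4 | 3.0 | −16.2 | −15.0 | 85.0 / 70.3 / 69.2 |
| 0.65 | 8 | 2.0 | −16.6 | −15.9 | 83.9 / 64.6 / 57.9 |
| 0.65 | 8 | 3.0 | −24.4 | −21.0 | 83.9 / 59.6 / 54.6 |

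Monte Carlo error on the biases is about 1 to 3 points. The 0.65 rows are the relevant ones for power, because with death unrelated to slope they give 81%, close to the plan's 80%. The 0.50 rows start from 97%, which the plan does not claim. Simulated event shares were 34–39%, slightly below the plan's 40.5%.

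A separate simulation with its own assumed SDs gave estimates of 84% and 79% of truth at ratios of 2 and 3, and 99% with no link. With a 12-month window they were 89% and 85%.

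**4. Cross-check from the plan's own power.** Holding the standard error fixed, an attenuation *a* turns 80% power into Φ(2.80 × (1 − a) − 1.96). At a = 0.06 this is Φ(0.67) = 75%. At a = 0.24 it is Φ(0.17) = 57%.

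**The case against.** The strongest reply is that a likelihood-based mixed model is not naive about death. If death depends only on recorded values, the model is valid, and the simulated bias is indeed about zero when hazard and slope are unlinked. This stands: the bias is partial and conditional. What remains is that the plan neither states that assumption nor tests it for VC and strength, while declining to rely on it for ALSFRS-R.

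Other points stand as limits. Staggered entry does create variable follow-up by design, and 307–357 of 600 subjects have no event by month 39. The bias runs against the drug, so it does not manufacture a false benefit. The co-primary analyses and stopping rules are untouched.

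A reader might also infer more than the documents support:

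- **That every secondary outcome is affected.** Section 6.3.4 says quality of life does not track severity or progression, so the mechanism does not carry over to it on the plan's own account. Safety and tolerability are separate analyses, and time to refusal already uses a method allowing informative censoring by death.
- **That the long window is the cause.** The 12-month bias is nearly as large. Use of data to 36 months is itself inferred from the schedule and the rationale for the model, not stated for these outcomes.
- **That 49% is the relevant share.** That is the null figure. For a drug that works it is about 40%, and it includes tracheostomy and permanent ventilation, after which measurement could continue.
- **That telephone follow-up makes VC and strength unobtainable.** The telephone list ("vital status, adverse events, ALSFRS-R, review of ventilator status and mechanical ventilation record and study drug compliance check") omits both, but the same section offers home visits and section 6.2.3 reimburses staff travel. Some telephone-only loss remains possible.

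**Conclusion.** The point holds for VC and the dynamometry megascores only. Their planned analysis has no safeguard against death that depends on the unobserved slope, although the plan supplies one for ALSFRS-R and itself links these measures to survival. For an effective drug the slope benefit would be understated by roughly 6–24%. Power for the stated 17% effect would fall to about 60–75% in the simulation calibrated near the plan's 80%, or 57–75% by the direct arithmetic. Part of the simulated loss is simply fewer observations, which alone takes about 85% to 81%.

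These sizes rest on assumed SDs and slope–hazard ratios of 1.5–3 per SD, none of which the documents print. The direction is firmer than the size, and the bias vanishes if death is unrelated to slope. This is worth correcting, but it does not threaten the primary conclusions.

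**What to change.** Extend the shared-parameter model already specified for ALSFRS-R in section 9.1.3 (random slope plus Weibull time to death) to VC and the upper- and lower-extremity dynamometry megascores. Make it the main analysis or, at minimum, a prespecified sensitivity analysis, and report PROC MIXED alongside. State the data window and the missing-data assumption for these outcomes.

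Do not rely on a 12-month cut instead. It leaves most of the bias, keeps only weeks 4, 16, 32 and 48 after baseline, and gave slightly lower power (about 55–74% against 60–75%). Quality of life and safety need no change on this ground.

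The cost is modest programming, since the model is already planned, and reliance on a parametric survival assumption. Reporting both models lets readers see how much that assumption matters.

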To determine how large an effect on FVC and dynamometry we could detect, we calculated these parameters of this model from the placebo group of our 12-month topiramate study. We did not have dynamometry in that study so we substituted MVIC. Based on the estimates from this study we would have an 80% chance of showing significance at a two-sided  $p=0.05$  level if the true rate of change in the treatment group was a 17% decrease in the rate of decline of the outcome. Interestingly this was the same for all three of the outcomes. The analysis of the extent to which FVC and dynamometry are surrogates for time to death, tracheostomy and PAV will be conducted using the methods of Shah and colleagues [190].

***Analysis of Data on Women and Minorities.*** Our proposal for the analyses of these data follows NIH Guidelines. We intend to use the data from the trial to determine whether women or minorities respond differently to treatment. This will be accomplished by testing for a treatment gender and treatment ethnicity interaction in our efficacy and safety analyses. Although the power of these analyses may be low for the primary outcome the power will be adequate for the secondary outcomes.

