### **11.3 Inclusion of Women**

The gender distribution for subjects with sporadic ALS is approximately 60% male and 40% female. The study goal is to recruit men and women with ALS in a 3:2 ratio. The MGH patient population includes 53% men and 47% women. Subjects at participating sites will be recruited from those site-specific areas and their surrounding communities. Special efforts will be employed to recruit female subjects. Advertising the study with several ALS and MND foundations will aid in the recruitment process, and in particular with the recruitment of female subjects.

The sites in the proposed study have demonstrated the ability to enroll females in prior NEALS and industry-sponsored studies. In the NEALS multi-center topiramate trial in ALS, 36% of the subjects were female. Similarly in the NEALS clinical trial of creatine in ALS and in the clinical trial of celebrex in ALS, 39% and 36% of the subjects were female, respectively. Each site has provided detailed enrollment goals and all sites documented ability to enroll 40% females. Copies of these documents are kept at the MGH Coordination Center. Based on this information, we do not anticipate difficulty enrolling the number of females for this study that represents the percentage of females with ALS in the total population.

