### **11.4 Inclusion of Minorities**

ALS is a relatively rare disease and there is mixed data on its incidence in minority groups. Most epidemiologic studies of ALS have investigated homogeneous populations. One of the only mortality studies conducted within a large, multi-ethnic population by Annegers et al. (1991) found that age- and sex-adjusted mortality did not differ among ethnic groups [191]. Some studies suggest that ALS may be less frequent in non-white individuals. An incidence study in the state of Washington found rates in white males to be 1.8 per 100,000 compared to 0.74 per 100,000 per year for black males, although the difference was not statistically significant due to the small numbers of incident cases [8]. [name] recently determined the rates of ALS in whites, blacks and other racial groups in a cohort of US soldiers serving during the Gulf War I era. They concluded that the rate for ALS/MND in "Other racial groups" (mainly Hispanic) was significantly elevated compared to whites in this young, predominantly male cohort whereas the overall rate for blacks was 33% lower than the specific rates estimates [192].

Approximately 17% of the national population is of a non-white racial background. For the purposes of recruitment in this study we will assume a racial distribution similar to the overall US population. Ethnically, 12.5% of the national population is Hispanic or Latino (<http://www.census.gov>). Thus, the study goal is to enroll at least 12.5% of the subjects from this ethnic group. Approximately 13% of our nation's population is Black, 0.3% is Hawaiian/Pacific Islander, 4.2% is Asian, and approximately 1.5% is American Indian. Our goal is to enroll subjects with ALS that are representative of the nationwide demographics. The racial composition of MGH is 82% White, 3% Black, 1% Asian, and 12% unknown. The ethnic population of MGH is 3% Hispanic and 97% non-Hispanic. For geographical reasons, much of the local minority population does not have the MGH as its primary care facility in Boston.

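### Nothing supports the plan's assurance of adequate power for gender and ethnicity interactions on secondary outcomes; for a 17-point interaction on the slope outcomes, power would be about 28% (gender) and 15% (ethnicity)

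*Combined protocol and SAP*

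**What the plan says.** The paragraph on women and minorities in Section 9.1.3 (Analysis of Secondary Outcome Variables) commits to interaction tests of treatment with gender and with ethnicity, in both the efficacy and the safety analyses. Its purpose is to find out whether these groups respond differently. On power it says only: "Although the power of these analyses may be low for the primary outcome the power will be adequate for the secondary outcomes".

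The preceding paragraph of the same section holds the one quantified power statement for secondary outcomes. Using parameters from the "placebo group of our 12-month topiramate study", with MVIC standing in for dynamometry, it reports an "80% chance of showing significance at a two-sided" 0.05 level for a "17% decrease in the rate of decline of the outcome". It adds: "Interestingly this was the same for all three of the outcomes". This is a main effect of treatment in all subjects. The paragraph states no sample size, allocation ratio or standard deviation.

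Subgroup shares come from Section 11. Section 11.3 says: "The study goal is to recruit men and women with ALS in a 3:2 ratio", which is 40% women. Section 11.4 says: "Approximately 17% of the national population is of a non-white racial background". It separately gives 12.5% as the Hispanic or Latino share, and as the enrolment goal for that ethnic group.

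**The concern.** A main-effect test uses every subject to estimate one treatment difference. An interaction test compares two treatment differences, each estimated in only part of the sample, and the smaller part dominates the error. A trial sized to give 80% power for a main effect therefore has much less power for an interaction of the same size, and the loss grows as the minority share falls. Adequate power for the interactions cannot be inferred from the 17% figure, and nothing else in the plan supplies it.

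What is at stake is how a null result is read. These tests exist to say something about response in women and minorities. After a written assurance of adequate power, a non-significant interaction invites the conclusion that the groups respond alike. The primary comparisons are unaffected.

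**Working it through.** **Inputs from the plan.** Main effect 17 percentage points of the rate of decline, 80% power, two-sided 0.05 (Section 9.1.3). Shares f: 0.40 women (11.3), 0.125 Hispanic and 0.17 non-white (11.4). That the effect and the non-white share are both 17% is coincidence.

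**Assumptions.** The 17% figure refers to this trial. Variance and allocation ratio are the same in each subgroup. The interaction size is varied because the plan gives none.

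**The plan's own figure.** It cannot be reproduced independently, since neither the slope SD nor the number of placebo subjects behind it is given. It serves as an anchor:

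SE(main) = 17 / (1.960 + 0.842) = 6.07 points.

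With 600 subjects at 2:1 (the numbers stated for ALSFRS-R), this implies an SD of 6.07 / sqrt(1/200 + 1/400) = 70.1 points. Putting that SD back returns 80% power, which is circular and confirms only the algebra.

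**Interaction standard error.** SE(int) = SE(main) × sqrt(1/f + 1/(1−f)) = SE(main) / sqrt(f(1−f)). Sample size, allocation and SD cancel.

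**Power for a 17-point interaction.** Power = Φ(17/SE(int) − 1.960). The interaction detectable with 80% power is 17 / sqrt(f(1−f)).

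| Subgroup | f | SE multiplier | SE(int) | 17/SE(int) | Power | Points needed for 80% |
|---|---|---|---|---|---|---|
| Gender | 0.40 | 2.04 | 12.4 | 1.37 | 27.8% | 34.7 |
| Race, non-white | 0.17 | 2.66 | 16.2 | 1.05 | 18.2% | 45.3 |
| Ethnicity, Hispanic | 0.125 | 3.02 | 18.3 | 0.93 | 15.1% | 51.4 |

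**Four-cell check.** For gender, with 600 subjects, the cells are 80 and 160 women and 120 and 240 men. Then 70.1 × sqrt(1/80 + 1/160 + 1/120 + 1/240) = 12.4, as above. The same check reproduces the other two rows.

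**Range over the unstated interaction size** (both tails counted):

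| Interaction | Gender | Race (17%) | Ethnicity (12.5%) |
|---|---|---|---|
| 8.5 points | 11% | 8% | 8% |
| 17 points | 28% | 18% | 15% |
| 25.5 points | 54% | 35% | 29% |
| 34 points | 78% | 56% | 46% |

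**Other sensitivities.** Section 11.3 also cites female shares of 36% to 47%, which move the 17-point gender figure only between 27% and 29%. A one-sided 0.05 test would give 39% (gender), 28% (race) and 24% (ethnicity).

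**What 80% power requires.** Take an average slowing of 17% and a gender interaction of 34.7 points with 40% women. The effect in men is then 17 + 0.4 × 34.7 = 31% slowing, and in women 17 − 0.6 × 34.7 = −4%, a slightly faster decline.

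**The case against.** The strongest reply is that power depends on the interaction size, and the plan names neither a size nor a numerical power. A reader might infer that the plan's own figures imply 28% and 18%. They do not: choosing an interaction equal to the main effect is an assumption made here. The topiramate results in Section 6.3.4 show that large slope differences occur. Arm strength fell by 0.1 units per month on drug against 0.075 on placebo, about 33% faster. A gender interaction of that size would have power of about Φ(33.3/12.4 − 1.960) = 77%. This stands as a reason to show the range. It does not establish adequacy, because that difference is a main effect, and ethnicity power is still below 50% at 34 points.

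A reader might also attach 18% to the planned ethnicity test. That figure rests on the racial share; the plan's ethnic share is 12.5%, which gives 15%. How ethnicity will be coded is not stated.

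Scope is a fair limit too. The 17% figure was derived for FVC and dynamometry, with a third outcome mentioned but not identified. Quality of life is not shown to be covered, and the calculation says nothing about interactions on safety outcomes. Attaching 600 subjects to the 17% is an inference from the ALSFRS-R paragraph, although the number cancels if the figure refers to this trial.

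The plan does concede low power for the primary outcome, and the secondary slopes are more sensitive than ALSFRS-R: the detectable gender interaction is about 35 points against 25 × 2.04 = 51 for ALSFRS-R. That supports better power, not adequate power. Finally, nothing in the plan says that a null interaction will be taken as equal response, and no dosing or stopping decision depends on these tests. The misreading is a risk that the wording invites, not a stated intention.

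**Conclusion.** The concern holds as an unsupported statement about power; no stated figure is miscalculated. For the vital capacity and strength slopes, if the 17% figure describes this trial, variances are equal across subgroups and the interaction equals 17 points, power is about 28% for gender, 15% for ethnicity and 18% for race. The tests reach 80% only when the interaction is about 2.0 (gender), 3.0 (ethnicity) or 2.7 (race) times the main effect that the trial can detect with that power. Since the plan names no interaction size, the range belongs with these figures. The documents do not support extending the finding to safety outcomes. The sentence should be changed because it limits what the trial can conclude about women and minorities, but the primary inference is untouched.

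**What to change.** Replace the sentence on adequate power with the computed power, or with the interaction detectable at 80% power, for the slope outcomes; give the assumed subgroup shares and interaction size. State whether the minority test uses race, ethnicity or both. Label the interaction tests exploratory for primary and secondary outcomes alike. Report each subgroup effect and each interaction with a 95% confidence interval, and say in advance that a non-significant interaction will not be read as equal response.

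The cost is a short text change and minor extra output, and a stated property of the design becomes less favourable. Sample size, randomization and the primary analyses stay as they are.
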